#### **D) Power/Sample Size Estimate:**

Expected Recruitment: At the time of this application we are collaborating with multiple ICCER-affiliated LTC organizations that wish to participate in this initiative. Most of these organizations have multiple facilities, many of which have multiple buildings or wings. Using Canadian Primary Care Sentinel Surveillance (CPCSSN) EMR data (accessed for the purpose of this application) we know that 53% of Canadians 80 yrs and older are listed as currently taking daily BP lowering medication. In our experience most of these medications are maintained upon nursing home admission. This suggests, given the 18-month median lifespan of newly admitted patients (and 9 month median lifespan of those already resident at the time of the study), that we should easily obtain 1200 residents total over the roughly 2-3-year duration of the trial.

Power: Utilizing well described methods for sample size determination, inflating the number of events to account for noncompliance, conservatively setting the median lifespan at 3 years to account for the inclusion of supportive living residents who, on average, live longer than the expected 18 months in long-term care facilities and assuming 33% of patients will be censored prior to any events, we find that 1232 patients would have 80% power (at a p of 0.05) to detect a difference between groups in the primary outcome of 27.6%. Although smaller differences would still be clinically meaningful, this difference is less than the 55% relative reduction in total mortality claimed in the MAPEC trial that we are trying to reproduce, and it is a very conservative minimum estimate for the actual power that the study will have. Additional power, while not directly calculable, will come in 2 ways: 1) These calculations assume no meaningful covariates and we have several covariates that are likely to be predictive of each outcome – in particular the resident's

level of care designation, and 2) we will continue to seek new facilities to partner with over the course of the trial – which should increase the number of residents available.

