# BedMed-Frail Statistical Analysis Plan

## **Adaptive Randomization (conversion to modified intention-to-treat)**

Participating facilities are volunteering to support our trial with no financial compensation, and “fitting it in” with other work. For several facilities, COVID-19, other infectious outbreaks, and implementation of other facility initiatives has led to long delays before the facility pharmacist was able to act on their allocation list. For a few facilities this delayed implementation by several months. Given 1) we are placing an equal emphasis on detecting harm, 2) long implementation delays make both groups look more similar and reduce the ability to detect harm, and 3) no action of any kind was taken related to the facility’s allocation list in this interval, we have adapted the trial to consider the date of each facility’s initial randomization to be the date the allocation list was actually acted upon, and not the date it was generated. This date was determined by the AHS data analyst, using electronic pharmacy dispensing data, to be the day before the first switch of an eligible patient’s BP medications from morning to bedtime. Individuals who, on the date of implementation, were no longer resident in the facility, hospitalized, or without once daily BP meds, were excluded from the trial.

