### *Secondary Safety:*

1. Non-vertebral fracture
2. Fall in the last 30 days\*
3. Urinary incontinence ( $\geq$  “occasionally incontinent” = 2 or more times per week)\*
4. Partial or full thickness decubitus skin ulceration (i.e. stages 2 to 4)\*

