### *Cognitive / Behavioral*

5. “Deteriorated cognition relative to status 90 days prior”\*
6. “Behavioral symptoms that are present a minimum of 4 days per week and not easily altered in the last 7 days” (includes wandering, verbal abuse, physical abuse, socially inappropriate or disruptive behavior, and resisting care)\*

7. Receipt of antipsychotic medication or physical restraints (chair, trunk, or limb restraints, does not include bedrails) in the last 7 days\*
8. Receipt of anti-anxiety medication on  $\geq 3$  of the last 7 days\*
9. Receipt of a bedtime sleeping pill on  $\geq 3$  of the last 7 days\*
10. “Indicators of depression or anxiety almost daily” in the last 30 days (applies to 16 discrete mood and anxiety related observations of the resident, any one of which being listed as present 6 or more days per week would qualify)\*

\* Safety outcomes 2 – 10 will only be examined in LTC residents (and not Level 4 or 4D residents), as these measures are not as regularly collected on those who reside in facilities with a lower level of care. Each are binary outcomes as recorded by usual care nurses in the Quarterly RAI-MDS report in the 3- to 6-month window post-randomization (on average these assessments should take place roughly 135 days post-randomization, and the assessment closest to 135 days is chosen when more than one is available)

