## **Statistical Analysis**

### **Intension-to-treat assumptions**

*Loss to follow-up:* If participants change continuing care facilities within Alberta, we will no longer be able to control their medication timing, which is likely to default to morning use upon entering a new facility. As such, we will censor residents who change facilities on the first day of residence in the new continuing care facility. However, we will not censor patients transferred to “inpatient LTC” at a local hospital, as that is likely to represent an escalation in care due to acute illness, or diminished capacity. If such individuals improve, they may return to the original continuing care facility and we can continue to follow them. If not, the transfer to “inpatient LTC” likely signals a

deterioration of health that may precede adverse health outcomes that would be important to capture. If residents change their level of care, but remain in the same facility (i.e. move to a different floor, or wing, which has a different level of care), we will continue to follow them, as their medication timing is unlikely to change.

*Withdrawal:* Residents who do not want to participate in BedMed-Frail are generally “opted out” (i.e. excluded) prior to randomization. Should we be approached, by a resident, their family, or their providers, to opt-out a resident after randomization, that is likely to be prompted by an attempted timing change, and hence a more likely occurrence for those allocated to bedtime. To avoid the introduction of attrition bias, all post-randomization opt-outs will be included and analyzed per their allocation unless we are explicitly asked not to follow their electronic health data.

*Missing MDS data:* For each analysis, we will use the post-randomization MDS nursing report closest to day 135 (tie going to the later date). If there are no such post-randomization reports we will use the report immediately preceding randomization. If no reports of any kind are available (which should not occur as a baseline MDS report is a routine part of every admission), we will exclude the participant from the analysis.

*Nonadherence:* Nonadherence to allocation will not exclude participants from any of our planned analyses. However, as outlined in Sensitivity Analysis below, we will conduct a per-protocol analysis to determine whether results differ when adherence to allocation is highest.

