| Secondary Safety (non-cognitive)                                             |                          |                                                                                                                                                                                                                                                                                                                                |
| Non-vertebral fracture                                                              | Cox Proportional Hazards | Facility/Level of Care specific non-vertebral fracture rate (prior 3 years), prior non-vertebral fracture, Gender, Age < 70, New admission*, Old admission †                                                                                                                                                        |
| Fall in the last 30 days                                                            | Poisson Regression       | Facility/Level of Care specific prior % fallers ‡ , Facility/Level of Care specific non-vertebral fracture rate (prior 3 years), New admission*, Old admission † , Gender                                                                                                                                |
| Urinary incontinence                                                                | Poisson Regression       | Facility/Level of Care specific prior % incontinent ‡ , New admission*, Old admission † , Age < 70, stroke, gender, diabetes                                                                                                                                                                             |
| Full thickness skin ulceration (stage 3 or 4)                                       | Poisson Regression       | Facility/Level of Care specific prior % ulcerated, ‡ New admission*, Old admission † , Stroke, Number of BP medications, Age < 70, gender                                                                                                                                                                |

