| Cost                                                                                                                                                                                                                                                                                                                                                                                  |                            |                                                                                                                                                                                                                                                                                                            |
| Acute care costs

Total cost of care                                                                                                                                                                                                                                                                                                                                                   | Multiple Linear Regression | Facility, Level of Care § , Age <70, New admission*, Old admission † , Gender, Days hospitalized in prior 6 months, Number of ED visits in prior 6 months, Charlson score, Total number of non-BP medications, Total number of BP medications, CHF, COPD, diabetes, CAD, stroke, CKD |
| * Resident in current facility less than 60-days at time of randomization
† Resident in current facility more than 3-years at time of randomization
‡ % of all RAI-MDS reports from this facility over the last 3-years indicating this outcome
§ In order of increasing care, this includes: Levels 3, 4, 4D, and 5 (as described in the manuscript under Setting and Recruitment) |                            |                                                                                                                                                                                                                                                                                                            |

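### The urinary incontinence model omits the resident's own pre-randomisation continence, which the RAI-MDS data already hold, and so gives up precision on a harm outcome

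*Combined protocol and SAP*

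**What the plan says.** Urinary incontinence is outcome 3 under Secondary Safety in the SAP, counted as present from "occasionally incontinent” = 2 or more times per week". The footnote to safety outcomes 2 to 10 restricts it to LTC residents and adds: "Each are binary outcomes as recorded by usual care nurses in the Quarterly RAI-MDS report", within 3 to 6 months of randomisation.

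Table 2 gives the method as Poisson regression. The covariates, in order, are "Facility/Level of Care specific prior % incontinent", new admission, old admission, age under 70, stroke, gender and diabetes. A table footnote defines the first as the percentage "of all RAI-MDS reports from this facility over the last 3-years indicating this outcome". None of the seven is the resident's own earlier continence. The fracture row, by contrast, does include the resident's own prior fracture.

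Under Missing MDS data the SAP says that "a baseline MDS report is a routine part of every admission", and also: "If there are no such post-randomization reports we will use the report immediately preceding randomization". A resident's earlier continence can therefore stand in as the outcome but is never a covariate.

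Neither document names a robust, sandwich or log-binomial method. In the section on adaptive randomisation, one reason given for re-dating randomisation is that "we are placing an equal emphasis on detecting harm".

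**The concern.** A resident's own continence before randomisation should predict status near day 135 better than the average of the facility does. Leaving out a strong predictor does not bias a randomised comparison, but it leaves avoidable between-resident variation in the error and widens the confidence interval. For a harm outcome the risk is that an imprecise null result is read as reassurance.

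The unnamed variance estimator matters for the same reason. A Poisson model takes the variance of the outcome as p, while a yes/no outcome has variance p(1 - p). Model-based errors are then too wide, most of all when the outcome is common.

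**Working it through.** **1. The plan's own power figure.** The only one concerns the primary outcome: 4 × (1.960 + 0.842)² / (ln 0.724)² = 4 × 7.85 / 0.1043 = 301 events, as stated in the protocol. No power is given for urinary incontinence. The number of LTC residents, prevalence, persistence, recording error and effect size are also absent, so every input below is assumed.

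**2. Closed form.** Take n = 300 per arm, prevalence p = 0.60, and correlation r = 0.7 between own baseline and day-135 status. The standard error (SE) of the log rate ratio is:

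- correct, without own baseline: sqrt(2(1 - p)/(np)) = sqrt(0.8/180) = 0.067
- correct, with own baseline: 0.0667 × sqrt(1 - 0.49) = 0.048
- model-based Poisson: sqrt(2/(np)) = sqrt(2/180) = 0.105, essentially unchanged by adding baseline (0.106 in simulation).

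The variance is divided by 1/(1 - r²): 1.1 at r = 0.3, 2.0 at 0.7 and 5.3 at 0.9. Model-based errors are too wide by 1/sqrt(1 - p): 1.41 at 50%, 1.58 at 60% and 2.24 at 80%. At 60%, a nominal 5% test then rejects only beyond 1.96 × 1.58 = 3.10 true standard errors, an actual error of about 0.002.

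Simulated power for a rate ratio of 1.10 in this setting rises from 34% to 53% with robust errors when own baseline is added. With model-based errors it falls from 5% to 1%, because the estimate varies less while the reported error stays as wide. The two changes therefore have to be made together.

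**3. Simulation with recording error.** Assumptions: 300 per arm, 20 facilities, four continence levels (the documents do not give the number of levels), one-level worsening of 10% versus 20%, improvement 5%, and facility % incontinent in both models. Misrecording shifts 20% of readings by one level. Carry-forward gives 20% of residents their recorded baseline as outcome. Power with robust errors, planned model then with own baseline:

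| Below the cut at baseline | 50% | 40% | 30% | 20% |
|---|---|---|---|---|
| Error-free | 25 to 66% | 18 to 56% | 14 to 44% | 10 to 29% |
| Misrecording | 16 to 23% | 13 to 19% | 10 to 15% | 8 to 12% |
| Misrecording and carry-forward | 12 to 17% | 9 to 15% | 8 to 12% | 7 to 9% |

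With no treatment effect, own baseline divides the variance by 4.8 to 6.1 (error-free), 1.6 to 1.8 (misrecording), and 1.8 to 2.1 (misrecording and carry-forward). Part of the last figure is artificial, because a carried-forward outcome comes from the same report as the covariate. If end levels are misread half as often, the two noisy ranges become 2.0 to 2.3 and 2.5 to 2.8. Type I error with robust errors is 4.2 to 5.8%. Mean rate ratios with and without own baseline agree within 0.002, so the quantity estimated does not change.

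**4. Carry-forward share.** The protocol cites a "9 month median lifespan of those already resident at the time of the study". With exponential survival, 1 - 2^(-3/9) = 20.6% die before month 3; an 18-month median gives 10.9% and 36 months 5.6%. That assumes only a report from month 3 onwards counts. If any post-randomisation report counts and first reports are spread evenly over three months, the 9-month figure is 1 - [9/(3 ln 2)] × 0.206 = 10.7%. The SAP can be read either way, so 20% is an upper value.

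**The case against.** The strongest reply is that this is a preference about efficiency and not an error. The SAP fixes an ordered, capped covariate list with no stepwise selection, and the outcome is one of ten secondary safety outcomes, in LTC residents only. The large gains need near-perfect recording by usual-care staff. Nonadherence shrinks them further: if only 60% of bedtime residents experience the effect (10% versus 20%, 50% below the cut), power goes from 11% to 30% with perfect recording, and only from about 7% to 8% with misrecording and carry-forward. On that view the test is uninformative with or without the covariate.

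Much of this stands. The gain may be small and power may stay low. The standard-error part also rests on silence: an analyst who uses sandwich errors loses nothing there. A reader might infer that the SAP prescribes model-based errors, so that the harm test can hardly reject. The documents do not support that, since they name no estimator.

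The reply does not reverse the direction. Own baseline improved power in every simulated setting with robust errors, and the value comes from a report the plan already uses.

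**Conclusion.** The point holds as an avoidable loss of precision on one LTC-only secondary safety outcome. Under the assumptions shown, own baseline divides the variance of the log rate ratio by about 1.5 to 2 with noisy recording and about 5 with error-free recording. The gain depends on robust errors being used.

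A reader might go further and conclude that the incontinence comparison is biased, or that the plan has been shown to fail on harm. Neither follows. Randomisation protects the comparison, the primary result is unaffected, and the inputs needed to size the loss are not in the documents. The change is worth making because it costs little and fits the SAP's stated emphasis on harm.

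**What to change.** In the urinary incontinence row of Table 2:

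1. Make the resident's own pre-randomisation MDS continence the first covariate, either as the binary status at the same cut or as the recorded level if the covariate cap allows.
2. State Poisson regression with robust (sandwich) standard errors, adopted together with item 1.
3. Keep residents who lack a pre-randomisation report by giving them a missing-indicator category. Report by arm how many outcomes were carried forward, with a sensitivity analysis excluding those residents. That exclusion depends on what happened after randomisation, so it is supportive only.

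The cost is SAP wording and one or a few covariates under the limit of one per 10 outcomes. The seven listed need 70 outcomes; binary status plus a missing category makes nine terms, or 90. At an assumed 300 LTC residents in all and 50% prevalence, 150 outcomes allow 15. If the limit binds, later covariates drop out first. No new data or test is needed.

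Robust errors can sensibly cover all nine Poisson rows. Own baseline in the other status-type rows is a reasonable parallel change, but its gain was not quantified here.

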## **Outcomes**

Unless otherwise stated, all outcomes are recorded over the duration of the study.

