#### *Cost:*

1. Acute care costs (estimated from each hospital / ED admission’s resource intensity weight and length of stay)
2. Total cost of care (acute care costs + medication costs + physician billings + nursing / facility costs; with nursing / facility costs being estimated from level of care and duration of stay).

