### Selecting regression covariates

Analyses of dichotomous outcomes will use a maximum of 1 covariate per 10 outcomes, and analyses of continuous outcomes will use a maximum of 1 covariate per 20 randomized subjects. The covariate list for each analysis is predefined in table 2, and all are measured at baseline. We will always use the maximum number of covariates possible, selected in the order given (i.e. we will not undertake stepwise addition or subtraction). As we go down the covariate list, if one covariate has too many levels to be accommodated by the remaining number of outcomes or participants (e.g. facility, or level of care) we will skip it and go to the next covariate in the list.

| Table 2 Analysis Plan        |                          |                                                                                                  |
|-------------------------------------|--------------------------|--------------------------------------------------------------------------------------------------|
| Outcome                      | Method            | Baseline Covariates                                                                       |
| Primary                      |                          |                                                                                                  |
| Major adverse cardiovascular events | Cox Proportional Hazards | Age <70, Gender, Facility/Level of Care specific mortality rate (prior 3 years), New admission*, |

|                                                                                     |                          |                                                                                                                                                                                                                                                                                                                                |
|-------------------------------------------------------------------------------------|--------------------------|--------------------------------------------------------------------------------------------------------------------------------------------------------------------------------------------------------------------------------------------------------------------------------------------------------------------------------|

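### The cost models omit entry date or potential follow-up, which loses precision for total cost of care, and total cost is not reported apart from survival

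*Combined protocol and SAP*

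**What the plan says.** The SAP's Outcomes section sets the window: "Unless otherwise stated, all outcomes are recorded over the duration of the study". Neither cost outcome states otherwise, so both are cumulative. Under the Cost heading, acute care cost comes from each admission's "resource intensity weight and length of stay". Total cost adds medication, physician and nursing/facility costs, "with nursing / facility costs being estimated from level of care and duration of stay".

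Table 2 gives "Multiple Linear Regression" for both outcomes, with 17 listed covariates. The list runs from Facility and Level of Care to "Total number of non-BP medications, Total number of BP medications, CHF, COPD, diabetes, CAD, stroke, CKD". It contains no entry date, potential follow-up or exposure term. The SAP says of its covariates that "all are measured at baseline". Neither document gives a fixed horizon, a rate per day, or weighting for incompletely observed costs.

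Follow-up is unequal by design:
- Each facility's start is the date its allocation list was acted on (SAP, Adaptive Randomization).
- New residents keep becoming eligible (Protocol, Statistical Analysis).
- Everyone stops when 301 events are reached (Protocol, Study Follow-up).
- Residents are censored on moving to another continuing care facility (SAP, Loss to follow-up).

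Objective C in the protocol concerns acute care costs only. Total cost of care appears only in the SAP.

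**The concern.** A resident observed for two and a half years can accrue far more cost than one who enters three months before the stop. Much of that spread reflects entry date, which is known at time zero and cannot be affected by allocation. Leaving it in the residual widens the interval for the arm difference for no gain. The Cox models for clinical outcomes handle unequal follow-up; the cost regression has no counterpart.

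The second issue is interpretation. Nursing/facility cost depends on duration of stay, so it ends at death. An arm with more deaths has fewer paid days and a lower total even if every day alive costs the same. The SAP places equal emphasis on detecting harm, and death is part of the primary outcome. A total-cost figure presented alone could turn a mortality harm into an apparent saving.

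**Working it through.** The documents give no mean, SD or power for cost, so there is no cost figure to reproduce. The nearby figure is the event target. A 27.6% reduction is a hazard ratio (HR) of 0.724, and 4 × (1.95996 + 0.84162)² / (ln 0.724)² = 4 × 7.8489 / 0.10431 ≈ 301, as stated. Nothing below changes it.

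**1. Total cost and survival.** Inputs from the protocol's power section: median lifespan of 9 months (existing residents), 18 months (new admissions) or 3 years (power calculation), and a trial of roughly 2–3 years. Assumptions: exponential survival with hazard λ = ln 2 / median, potential follow-up uniform on 0 to τ years, and the same cost per day alive in both arms. Mean cumulative cost is then proportional to mean observed stay:

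E[min(T, C)] = (1/λ) × [1 − (1 − e^(−λτ)) / (λτ)]

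Example, median 1.5 years and τ = 2.5:
- Reference arm: λ = 0.4621 and λτ = 1.1552, so the mean stay is 0.8808 years.
- Death HR 0.85: λ = 0.3928 and λτ = 0.9820, so the mean stay is 0.9244 years.
- Ratio: 0.9244 / 0.8808 = 1.049.

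| Median survival | τ | Reference stay (y) | Stay at HR 0.85 (y) | Change at HR 0.85 | Change at HR 1.15 |
|---|---|---|---|---|---|
| 36 months | 2.5 | 1.0404 | 1.0683 | +2.7% | −2.6% |
| 36 months | 3 | 1.2060 | 1.2442 | +3.2% | −3.0% |
| 18 months | 2.5 | 0.8808 | 0.9244 | +4.9% | −4.6% |
| 18 months | 3 | 0.9933 | 1.0503 | +5.7% | −5.3% |
| 9 months | 2.5 | 0.6602 | 0.7157 | +8.4% | −7.4% |
| 9 months | 3 | 0.7162 | 0.7840 | +9.5% | −8.1% |

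Cost per day alive is identical in every row.

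**2. Acute cost.** Let ordinary acute cost accrue evenly while alive, and let a death add k years' worth of it. The probability of an observed death is λ × E[min(T, C)], so the mean is E[min(T, C)] × (1 + kλ). Take τ = 3, a 3-year median and a death HR of 0.724 between arms:
- k = 0: 1.206 against 1.278. The arm with more deaths is 5.6% cheaper.
- k = 1: 1.485 against 1.491, 0.4% cheaper.
- k = 2: 1.763 against 1.705, 3.4% dearer.

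At an 18-month median the results are 9.9% cheaper, 1.3% cheaper and 3.9% dearer. The sign turns on k, which the documents do not give.

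**3. Precision with planned covariates in the model.** I simulated 16 facilities with starts spread over 1.5 of 3 years. Between 30% and 70% of residents entered at the facility's start and the rest later. Median survival was 0.75–3 years. Facility and a new-admission indicator were fitted first, then potential follow-up and its square. All of this structure is assumed. The further residual variance removed was:

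| Outcome | Variability assumed | Further variance removed |
|---|---|---|
| Total cost | daily-cost CV 0.2 | 4.6–34.5% |
| Total cost | daily-cost CV 0.5 | 3.1–19.6% |
| Total cost | daily-cost CV 1.0 | 1.5–7.6% |
| Acute cost | 0.5 admissions/year, gamma frailty, cost CV 1–2 | 0.2–2.6% |

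The best total-cost case cuts the standard error by 1 − √(1 − 0.345) = 19%, and the weakest by about 1%. The best acute case cuts it by 1 − √(1 − 0.026) = 1.3%. The square adds at most about 1.6 percentage points of variance over a linear term.

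**4. Covariate room.** The limit is "analyses of continuous outcomes will use a maximum of 1 covariate per 20 randomized subjects", so 1200 / 20 = 60 terms. Fifteen single-term covariates, 3 for the four levels of care and 2 for potential follow-up make 20. That leaves 40 for Facility, enough for 41 facilities.

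**The case against.** The strongest reply is that nothing here biases the analysis. Potential follow-up is balanced by randomisation, the interval for cumulative cost stays valid, and lower spending after earlier death is real spending that a payer may want to know. All-cause mortality is a listed secondary outcome, so a mortality harm would be reported anyway. Table 2 also already includes Facility, which absorbs facility start dates, and New admission, which picks out many later entrants. All of this stands, and it limits the point to precision and interpretation. The two covariates capture entry only in part: a 60-day indicator does not say when in the trial a resident joined.

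A reader might infer four stronger things that the documents do not support:
- **That an arm with more deaths will look cheaper on both cost outcomes.** This holds for total cost under equal daily cost. For acute cost, terminal admissions can reverse it.
- **That Objective C is seriously compromised.** It covers acute care costs only, where the precision gain is small.
- **That a follow-up term would remove the death effect.** Potential follow-up is the same in expectation in both arms, so it restores precision and leaves the survival difference untouched.
- **That the precision gain is uniformly large.** With uniform entry over 0–3 years, daily-cost CV 0.2 and no other covariates, potential follow-up removes 32–49% of variance. That ignores Facility and New admission, and at CV 2 the figure falls to 3–4%.

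**Conclusion.** The point holds as a modest one. Both cost models leave out a strong, freely available baseline predictor of cumulative cost. For total cost of care this leaves roughly 2–35% of residual variance unexplained beyond Facility and New admission, for daily-cost CVs of 0.2–1.0 and the assumed entry pattern. For acute care costs it is about 1–2%.

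Separately, total cost moves with survival. A death HR of 0.85 raises it by about 3–5% at median survival of 36 to 18 months (5.7% for 18 months in the 3-year window) and by up to about 10% at 9 months. An HR above 1 lowers it by similar amounts. This is a true difference in cumulative spending, but without a stated estimand it can be misread as efficiency.

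These sizes rest on exponential survival, uniform or assumed entry, and equal cost per day alive, none of which the documents give. The directions for precision and for total cost do not depend on the exact values. Cost is not the primary outcome, and the primary analysis and the 301-event target are unaffected.

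**What to change.** In SAP Table 2, add potential follow-up (time zero to data cut-off, in days) near the top of the covariate list for both cost models, so that the fill-in-order rule cannot drop it. A linear term is equivalent to entry date, since the cut-off is common to all residents. A square may be added for a second slot. Do not use observed follow-up: it is affected by death and breaks the SAP's own baseline-only rule.

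In the Cost section, state that the estimand is cumulative cost to study end, and say how costs after a change of facility are treated, since the added covariate does not address that. Report total cost per resident-day alive and the mortality result beside the cumulative difference.

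The dates are already held. The price is one or two covariate slots and slightly more reporting.
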